## Abstract

**Background:**

Around 40 per cent of patients with unipolar depressive disorder who are treated in secondary care mental health services do not respond to first or second line treatments for depression. Such patients have 20 times the suicide rate of the general population and treatment response becomes harder to achieve and sustain the longer they remain depressed. Despite this there are no randomised controlled trials of community based service delivery interventions delivering both algorithm based pharmacotherapy and psychotherapy for patients with chronic depressive disorder in secondary care mental health services who remain moderately or severely depressed after six months treatment. Without such trials evidence based guidelines on services for such patients cannot be derived.

**Methods/design:**

Single blind individually randomised controlled trial of a specialist depression disorder team (psychiatrist and psychotherapist jointly assessing and providing algorithm based drug and psychological treatment) versus usual secondary care treatment. We will recruit 174 patients with unipolar depressive disorder in secondary mental health services with a Hamilton Depression Rating Scale (HDRS) score ≥ 16 and global assessment of function (GAF) ≤ 60 after ≥ 6 months treatment. The primary outcome measures will be the HDRS and GAF supplemented by economic analysis incuding the EQ5 D and analysis of barriers to care, implementation and the process of care. Audits to benchmark both treatment arms against national standards of care will aid the interpretation of the results of the study.

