### Design

A pragmatic single blind randomised controlled trial (RCT) of a specialist depression disorder intervention versus treatment as usual will be conducted. Participants will be individually randomised with stratification by mental health trust and allocated to each group on a one to one basis. Eligible participants will be followed for 24 months. The primary outcome will be observer rated depressive symptoms over the first 12 months but further analysis will explore if any differences in outcome are maintained at 24 months, 12 months after the patient has been discharged from the specialist depression disorder team. Figure 1 shows the overall design of the study.

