**Figure 1 F1:**
[figure not shown]
**Flow of patients in the randomised controlled trial of Specialist Mood Disorder Team versus usual care**.

The RCT forms part of the Nottinghamshire Derbyshire and Lincolnshire Collaboration for Leadership in Applied Health Research and Care (CLAHRC NDL), an applied health services research centre funded by the Department of Health, the University of Nottingham and nine health and social organisations in three English counties [18]. It focuses on service innovation and implementation of research as well as clinical and cost effectiveness of interventions that are perceived by the local health services to be a high priority.

Unlike traditional RCTs, which favour a small number of clinical outcomes, service delivery studies of complex interventions require multiple outcomes [19]. Service delivery studies are interested in a range of equally important outcomes including clinical outcome, cost effectiveness, access to services, burden on staff and risk of serious adverse events. Nevertheless, multiple outcome measures can lead to false positive conclusions about the effectiveness of a treatment so a primary outcome variable (change in depressive symptoms) is specified. In order to interpret the results of such a RCT, and identify important processes and context variables required for replication, a range of outcomes and process variables is necessary [19]. Therefore, alongside the RCT an implementation analysis of barriers and drivers to effective care using largely qualitative methods is performed. An audit will be performed of the standard of care delivered to the patient by secondary mental health care before and after entry to the study using NICE Guidelines for depression, the standard of care that is expected to be delivered in England and Wales [8,20]. The standard of care provided by the continuing treatment teams in the secondary care mental health services is important to measure in order to interpret the results of the RCT; if the standard of care is high in usual care, there may be ceiling effects operating even if the specialist depression disorder team is effective, but if usual care is poor then the specialist depression disorder team may be effective merely because it is providing an acceptable standard of care. In the latter case, the implication might be that better training and support for existing staff is required rather than the formation of a specialist depression disorder team.

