### Outcomes

**Primary outcome **measures are:

1. Longitudinal change in the 17-item observer rated Hamilton Depression Rating Scale (HDRS) [23,28] from baseline to 6 and 12 months as well as follow up assessments at 18 and 24 months. The primary analysis will be change over the baseline to 6 and 12 months. The purpose of the analysis at 18 and 24 months is to determine if any change is maintained once the patient has been discharged from the specialist depression disorder team.

2. Change in global assessment of function [24] from baseline to 6 and 12 months as well as follow up assessments at 18 and 24 months.

**Secondary outcome **MEASURES ARE:

1. Change in self-rated depression: a) self-rated Beck Depression Inventory version 1 [29], a measure of cognitive symptoms of depression from baseline to 3, 6, 9, 12, 18 and 24 months; b) Personal Health Questionnaire [30] from baseline to 3, 6, 9, 12, 18 and 24 months, rating of depression severity according to DSM-IV criteria; c) Quick Inventory for Depressive Symptomatology self rated version [31] from 3, 6, 9, 12, 18 and 24 months, a 16-item screening/diagnostic questionnaire rating depression severity according to DSM-IV criteria. The last scale has the best established psychometric data for remission compared to the Hamilton Depression Rating Scale. The other two scales are widely used in clinical practice by general practitioners and psychotherapy services in England and Wales.

2. Euroqol 5 D [32] as a measure of quality of life and costs from health and social care and society perspectives measured at 6, 12, 18 and 24 months. Use of the EQ5 D will enable utility score sto be gained from the patients that may then be used in a cost utility analysis

3. Change in social adjustment [33], an assessment of social and occupational functioning from baseline to 6, 12, 18 and 24 months.

4. Patient satisfaction and relationship with the clinician(s) on a four part 9-item questionnaire based on two other questionnaires used frequently in depression studies: the Patient Satisfaction Questionnaire [34] and the Patient Doctor Relationship Questionnaire [35]. These will be measured at 6, 12, 18 and 24 months.

**Process measures**, which will not be utilised to determine the effectiveness of the interventions, but will be used to understand the processes that are taking place:

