### Statistical analysis

Statistical analysis for quantitative measures will be on the 'intention-to-treat' basis and carried out by the research team in two stages. At the first stage, analysis will be focused on process measures. Differences at each time point and in changing patterns over time between the two treatment groups and amongst clinical sites will be examined. Results from such analysis will help us to identify possible covariates or confounders at the individual level or clinical level that may need to be adjusted for when comparing the primary of secondary measures between treatment groups. Mechanism of missing data on major outcomes will be examined by sensitivity analysis, to inform adequate imputation procedures. At the second stage, the HDRS of the primary measure as well as multiple secondary measures will be analysed separately and jointly. As all measures are taken longitudinally, multilevel models for repeated measures will be used [49]. Data of patients who dropped out or not completed follow-up measures will be analysed in the manor of last-observation-carried-forward in multilevel modelling. The core model for each measure will be two-level with individuals as level 2 units and time occasions as level 1 units. If random effects or large variation among clinical sites are detected in the first stage analysis, the core model will be extended to three-level with clinical sites at the top of the hierarchy as level 3 units to account for random effects among clinics. For analysing multiple measures (or multiple end points) simultaneously to investigate global change or multi-dimensional change of the intervention effects, the core model will also be extended to a three-level structure with measures at the bottom of the data hierarchy. All models will estimate the mean changes of measures from the baseline to the later time points for each treatment group, and differences in such changes between groups by interaction terms between time and treatment group in models, adjusting for possible confounders or covariates. For continuous measures with reasonably symmetric distribution, ordinary multilevel models will be used in the analysis. Otherwise, data transformation before model fitting will be considered. For count data with a long tail in the distribution, multilevel Poisson models will be considered [50]. For ordinal measures, multilevel multinomial models will be considered [51]. Descriptive and simple statistical analysis will be performed in SPSS and MLwiN [52] will be used for multilevel models analysis.

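### The protocol names HDRS as the single primary outcome to guard against false positives, but the Abstract and Outcomes sections make HDRS and GAF both primary at one undivided 5% level

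*Protocol article*

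**What the plan says.** Three places point to one primary outcome.

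- Design, first paragraph: "The primary outcome will be observer rated depressive symptoms over the first 12 months".
- Design, text after Figure 1: having warned that several outcomes can produce false positive conclusions, the protocol continues "so a primary outcome variable (change in depressive symptoms) is specified".
- Statistical analysis: "the HDRS of the primary measure as well as multiple secondary measures will be analysed separately and jointly". GAF is not mentioned by name.

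Two places give two primary outcomes.

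- Abstract, Methods/design: "The primary outcome measures will be the HDRS and GAF".
- Outcomes: the primary list has HDRS as item 1 and GAF as item 2, the latter as "Change in global assessment of function [24] from baseline to 6 and 12 months", with follow-up at 18 and 24 months.

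On timing, item 1 (HDRS) adds "The primary analysis will be change over the baseline to 6 and 12 months". Item 2 (GAF) carries no such sentence. The Sample size section works throughout with a two-sided 5% level and 90% power, and does not divide the level between outcomes.

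**The concern.** The Design section gives a reason for having a single primary variable, and that reason is error control. Adding GAF to the primary list in the Abstract and Outcomes removes the safeguard without putting another in its place. If HDRS and GAF disagree at the end of the trial, one reader can cite the Design section and another the Abstract, and they will reach opposite conclusions on whether the primary objective was met.

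What is at stake depends on how two primaries would be used. If either one suffices, the overall false positive rate exceeds 5%. If both are required, the error rate is safe but the chance of success is lower than the power for one outcome.

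**Working it through.** **1. The plan's own figures.** Main calculation: 52 per group × 1.43 = 74.4, taken as 74; 74 × 1.18 = 87.3, taken as 87, or 174 in total. The 52 cannot be rebuilt because its effect size is not given. HDRS check: the 12-month scores give (11.3 − 5.9)/√((5.1² + 10.5²)/2) = 5.4/8.25 = 0.65, as stated. A two-sided t-test at 5% with 90% power then needs 50.7, so 51 per group; 51 × 1.2 = 61; 61 × 1.18 = 72, against 73 printed, a difference of no consequence here. Both chains use the full 5% for one comparison, so neither allows for a second primary outcome.

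**2. Either outcome suffices, one test each at two-sided 5%.** With independent statistics the familywise error is 1 − 0.95² = 9.75%. With correlation ρ it is 1 − P(|Z₁| ≤ 1.96 and |Z₂| ≤ 1.96) for a bivariate normal. The document gives no correlation between HDRS and GAF, so a range is assumed:

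| ρ (assumed) | Familywise error |
|---|---|
| 0 | 9.75% |
| 0.5 | 9.1% |
| 0.7 | 8.4% |
| 0.8 | 7.8% |
| 0.9 | 7.0% |

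**3. Both outcomes required.** The error rate stays at or below 5%. If each outcome had exactly 90% power, joint power would be 0.9 × 0.9 = 81% at ρ = 0, 83% at 0.5 and 86% at 0.8. For HDRS, however, the plan has a margin: 87/(1.18 × 1.2) = 61 evaluable per group, or 87 × 0.8/1.18 = 59 if a 20% loss is taken off the recruited number. At an effect size of 0.65 the t-test power is about 94.5% with 61 and 93.8% with 59. The power for GAF cannot be worked out from the document.

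**4. Level split in two (2.5% each).** The HDRS check would need 61 evaluable per group instead of 51. With 61 or 59 available, HDRS power is about 90.5% or 89.4%. For an outcome that had exactly 90% power with 87 per group at 5%, the required number rises by ((2.241 + 1.282)/(1.960 + 1.282))² = 1.18, to about 103 per group; with 87 retained, power falls to about 84%.

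**5. HDRS alone.** The level stays at 5% and the sample size is unchanged.

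**The case against.** The best reply is that the text favours HDRS: two statements in Design and one in Statistical analysis give it priority, and Outcomes lists it first with the only explicit sentence on the primary analysis. Multiplicity rules and the exact model contrast are also often left to an analysis plan, which is not shown here. Both points have force. They mean the absence of a testing rule is not in itself a fault, and that the repair is easy. They do not remove the contradiction, because the number of primary outcomes is stated in this document, in two incompatible ways.

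Several stronger readings are tempting, and the document does not support them.

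- **Four primary tests.** A reader might count two outcomes at two time points, each at 5%, which would give 18.5% if independent and about 9.3% at a common correlation of 0.9. But Design and Outcomes describe one longitudinal HDRS analysis covering 6 and 12 months. The Statistical analysis section speaks of time-by-treatment interaction terms without saying that each is tested separately. Four tests is an upper case, not what is written.
- **GAF was never powered.** The main calculation uses a global assessment of severity from a cited study. Whether that corresponds to GAF is not stated, so the claim can be neither made nor dismissed.
- **Joint power of 81% to 86%.** This sets HDRS power at exactly 90% and ignores the margin in step 3.
- **The lead result is open to free choice after the data are seen.** The priority given to HDRS in three places makes that too strong.
- **Month 6 should leave the primary analysis.** Design and Outcomes consistently place it inside, so the inconsistency gives no ground for removing it.

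**Conclusion.** The point holds as a conflict over the number of primary outcomes: one in Design and Statistical analysis, two in the Abstract and Outcomes, with a single undivided 5% level behind the sample size. On an either-outcome reading with one test per scale, the false positive rate would be about 7% to 10%. That range rests on assumed correlations from 0.9 to 0 and on jointly normal test statistics. It would be higher only if 6 and 12 months were also tested separately, which the text does not clearly say. The arithmetic leading to 174 is not in question, and with HDRS as sole primary outcome nothing in it has to change. The passages should be reconciled before any outcome data are examined by group.

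**What to change.** Amend the Abstract and the Outcomes section to agree with Design and Statistical analysis:

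- HDRS over the first 12 months is the sole primary outcome.
- It is tested once, at two-sided 5%, by a test from the longitudinal model named in advance. Two candidates fit the text: a joint group-by-time test over 6 and 12 months, or the 12-month contrast, which is the comparison used in the HDRS power check.
- GAF becomes the first key secondary outcome, tested at 5% only if HDRS is significant.

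The level stays at 5% and the target at 174. The cost is that GAF loses co-primary status. Because the Results section reports that recruitment is under way, this is a substantive change and needs a dated, documented amendment with its reason.

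If the sponsor prefers to keep both outcomes primary, it should state whether success means either or both, how the 5% is handled, and the power for that rule, including the effect size assumed for GAF.

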**Discussion:**

This trial will be the first to assess the effectiveness and implementation of a community based specialist depression disorder team. The study has been specially designed as part of the CLAHRC Nottinghamshire, Derbyshire and Lincolnshire joint collaboration between university, health and social care organisations to provide information of direct relevance to decisions on commissioning, service provision and implementation.

**Trial registration:**

Clinical trials.gov identifier NCT01047124

## Background

By 2020, unipolar depressive disorder is projected to be the second leading cause of disability adjusted life years in the world [1], and with anxiety accounts for one per cent of the whole gross national product of a wealthy country like United Kingdom [2]. Depressive disorder is associated with significant functional impairment that can be restored following effective treatment [3]. Depressive disorder is persistent [4], possibly due to the fact that people with depression often do not seek treatment following relapse; when they do, it is rarely effective [5]. A longitudinal pattern of frequent recurrences with increasing severity can occur which leads to social damage and possible neurobiological changes which may be difficult to reverse [4]. Moreover suicide after unipolar depression accounts for 0.7% deaths [6]. Patients with chronic unipolar mood disorder that has been diagnosed by health services have a standardised mortality ratio for suicide around 20 [7], constituting a high risk group for suicide already identified by mental health services.

While there is plenty of research showing the short-term effectiveness of antidepressant medication and psychological treatments such as cognitive behaviour therapy, there are few randomised controlled trials of service interventions for depressive disorders that do not respond to first-line or second-line interventions. As a result treatment guidelines refer to the need to consult a specialist in the assessment and treatment of mood disorders [8] but are not specific in their recommendation about the nature of such an intervention.

Previous research gives some indication of what might be achieved. The influential STAR*D project carried out at 41 service settings in the US involving 3,671 patients with non-psychotic unipolar major depressive disorder demonstrated that with 1 to 4 different acute treatments lasting at least 14 weeks, 67 percent of patients achieved remission over one year [9]. NICE Guidelines for depression advocate a combination of antidepressant medication and cognitive therapy for severe and chronic depression [8]. In a meta-analysis of patients with severe recurrent depressive disorders the overall response rate to cognitive behaviour therapy (CBT) or interpersonal psychotherapy combined with antidepressant management (ADM) was three times higher (63%) than to brief psychotherapy alone (20%) [10]. The combination of ADM and CT (45% remission) was also more effective than ADM (29% remission) in a RCT of 158 participants with residual treatment-refractory depressive symptoms at 18 months [11]. These differences in outcome persisted for up to 5 years [12]. Overall, the combination of individually tailored antidepressant treatment followed by augmentation strategies or combined with cognitive therapy that follow algorithms of evidence based research appear to be the gold standard of treatment for depression [8,13]. An active, coordinated and thoughtful approach is necessary when treating chronic and severe depression [4].

There is evidence that many patients with unipolar depression in secondary care mental health services may not receive such an approach [5]. In STAR*D where treatment was delivered under optimal conditions, 40 per cent of patients failed to respond to first or second line treatment s for depression [9]. When both antidepressant medication and cognitive therapy approaches are applied in the same patient, they may not be effective if the timing of the interventions is not complementary. For instance, a patient may be too sedated from drug treatment to attend properly to cognitive therapy or drug treatment is dismissed as ineffective before issues surrounding medication adherence are addressed through cognitive therapy or psychoeducation. Therefore, a co-ordinated approach involving joint assessment and management of patients who have not responded to first-line and second-line treatment approaches for depressive disorder in secondary care services is required. The addition of psychotherapy to treatment as usual in a mixed group of mental health patients who had not responded to first or second line treatment was seen to be cost effective [14]. However, this study did not explicitly examine patients with depressive disorder and the form of psychotherapy that was used is neither widely available nor tested specifically in patients with unipolar depression. A small RCT also demonstrated the effectiveness of in-patient interpersonal psychotherapy with pharmacotherapy over usual in-patient care for patients with chronic major depressive disorder [15]. There is a considerable amount of trial evidence for stepped care interventions for primary care depressive disorder where care is coordinated and the nature of the intervention is tailored to the individual [16], and also some evidence for out-patient algorithm based care mostly involving medication for major depression [9,17]. However, to our knowledge there is no previous randomised controlled trial examining the clinical and cost effectiveness of a community based specialist depression disorders team offering time-limited algorithm based pharmacotherapy and psychotherapy to patients with unipolar depressive disorder who remain moderately or severely depressed after six months treatment by secondary care mental health services.

## Methods/Design

### Objectives

1. To determine whether a community based specialist depression disorder team, offering time-limited algorithm based pharmacotherapy and psychotherapy, to patients with unipolar depressive disorder who remain moderately or severely depressed after six months treatment for depression is more clinically and cost effective than continuing treatment from their continuing care teams in the secondary care adult mental health service.

2. To identify barriers, drivers and important therapeutic constituents of clinical care that was effective in either the specialist depression disorder or continuing care teams.

### Design

A pragmatic single blind randomised controlled trial (RCT) of a specialist depression disorder intervention versus treatment as usual will be conducted. Participants will be individually randomised with stratification by mental health trust and allocated to each group on a one to one basis. Eligible participants will be followed for 24 months. The primary outcome will be observer rated depressive symptoms over the first 12 months but further analysis will explore if any differences in outcome are maintained at 24 months, 12 months after the patient has been discharged from the specialist depression disorder team. Figure 1 shows the overall design of the study.

